## 1. Introduction

Globally, 1.4% of disability-adjusted life years (DALYs) due to disease and injury in 2010 were from fall injuries, which were the third most important injury type following road injury and self-harm [1]. In New Zealand, falls accounted for 2.9% of DALYs, which was only slightly less than road injuries (3.1%) [2]. Between 2014 and 2016, there was an average of 544 unintentional deaths due to falls per year [3]. Between 2014 and 2018, in a population of 5 million there were more than 24,000 hospitalizations annually for unintentional fall injuries [3] and according to data provided by the Accident Compensation Corporation (ACC), between 2011 and 2018, there were an average of 658,000 falls annually requiring some form of medical treatment, of which more than half were at home (where the setting was defined).

Given the importance of the home as a setting for falls, the home environment is a potential focus of prevention efforts to install safety features or to remove hazards. However, randomized controlled trials focused on the safety benefits of home modification are rare. A meta-analysis of such trials found that home safety assessments, with subsequent modification, were effective in reducing the rate of falls among older people living in the community (rate ratio 0.81, 95% confidence interval (CI) 0.68 to 0.97; 6 trials; 4208 participants) [4]. Our previous study, the Home Injury Prevention Intervention (HIPI) randomized controlled trial, found a reduction in home fall injury rates of 26% (95% CI 6–42%) [5], although the study was not powered to look at specific groups, such as the Māori, the indigenous people of Aotearoa, New Zealand. As Māori suffer from poorer health on average than other New Zealanders, measures that may potentially reduce health inequalities, such as home modification to reduce fall risk, need to be identified. The aim of the current study was to assess the safety benefits of home modification specifically for Māori. The trial was designed to generate evidence for intervention that could be rolled out as a national programme.

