### 3.2. Outcomes

The primary outcome is rates of medically-treated unintentional falls per household per year. Secondary outcomes are medically-treated specific injuries (injuries that are potentially prevented by the treatment applied—see further details below) and costs of both these types of injuries, due to falls generally or due to the specific injuries. Costs are those borne by the health insurer, the ACC, as described above. Injury costs in relation to intervention costs will be analyzed to inform cost-benefit analyses of the intervention.

Rates will be estimated, firstly, for the MHIPI participants by themselves and, secondly, for the MHIPI participants plus all the Māori household members of the HIPI study, which shared an almost identical intervention. One important difference was that participants in the HIPI study consented to have the study team access their ACC injury records, which were assigned to individuals. To be consistent with the MHIPI data analysis, data for the Māori household members of the HIPI study will be aggregated to the household level.

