A sensitivity analysis will be conducted of the odds of falls and the odds of specific injuries compared to all other medically treated home injuries. This will enable models to be fitted that control for age group, which was found to be an important factor in the analytical models used in the analysis of the HIPI study [5]. Such an analysis will lose a proportion of information compared to the primary analysis of injury rates because households without any home injury claims over the assessment period do not contribute data. As the current intervention being tested was designed to prevent injuries arising from falls, it can be assumed that other types of injuries that occur in the home (burns, scalds, poisoning, cuts, stings, strains, collisions, etc.) would be relatively unaffected by the intervention. Using an odds ratio as an outcome measure has the additional benefit of controlling for propensity to seek—or to be differentially referred for—medical treatment following an injury, which is known to vary between different population groups, and to be lower for Māori than for others [7]. As randomization was carried out at the household level and stratified only at the regional level, there is always the potential for the intervention and control groups to differ at random, according to important characteristics associated with fall rates, such as age. Analysis of the odds of a particular injury type or mechanism compared to other injury types or mechanisms, is common in road safety for the assessment of vehicle-related safety characteristics, for example [9].

In order to detect a change of 26% in the percentage of households with medically-treated injuries arising from falls (α of 0.05, 80% power), we calculated that a sample size of about 125 households in each of the two arms of the study (treatment and control groups) would be required.

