This study, and the HIPI study that shared the same design, is limited in the way it can assess safety benefits separately for subsets of the intervention, i.e., particular types of modification carried out. This is because the study is designed to replicate the rollout of a potential injury prevention programme, which would take several effective interventions and apply them as a package. Such an approach is more efficient than doing each individual intervention separately, but it does limit our ability to assess individual aspects of the programme. Few specific types of modification were carried out in isolation, so inferences about safety effects of particular types of modifications are not feasible. For example, of the 436 homes modified in the HIPI study, on only one occasion was modification to the bathroom carried out without there being other modifications in the house [5]. Another limitation for assessing safety effects of specific modifications is that the treatment randomized was a package of modifications. Modifications within this package were not applied randomly, but were applied according to what was required. There are likely to be systematic differences between the behaviors, or individual factors, affecting fall risks of occupants of houses requiring a specific type of modification and houses not requiring that modification.

The current study is one of just a handful of randomized controlled trials on the safety benefits of home modification and the first study to our knowledge to focus on an indigenous population. We anticipate that the findings will provide evidence for effective injury prevention measures that can reduce an important aspect of health inequities.

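### The 80% power statement is for the percentage of households with a fall injury, not for the household rate that is the primary analysis, and the article's own figures do not support 80% for that rate

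*Protocol article*

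**What the plan says.** The last paragraph of section 3.2 before section 3.2.1 gives the sample size. It begins "In order to detect a change of 26% in the percentage of households with medically-treated injuries arising from falls (α of 0.05, 80% power"), and arrives at "a sample size of about 125 households in each of the two arms of the study". The endpoint is binary: a household has a fall injury or it does not. The paragraph does not state the control percentage, whether 26% is relative or absolute, or whether the test is one- or two-sided.

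The same section defines the endpoint differently: "The primary outcome is rates of medically-treated unintentional falls per household per year". Section 3.3.2 analyses it with a Poisson model for household counts, a log link and a log-time offset.

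The Introduction reports that HIPI "found a reduction in home fall injury rates of 26% (95% CI 6–42"%). That is the only other place where 26% appears, and there it refers to a rate.

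**The concern.** A 26% lower rate and a 26% lower percentage of households affected are different effects. If counts are Poisson, a rate ratio of 0.74 lowers the proportion of households with any fall by only about 19% to 22% at the fall frequencies derived below. Moving 26% from one scale to the other assumes a larger effect on the binary scale than HIPI's rate reduction implies. The stated power also belongs to a test that is not the primary one.

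What is at stake is how the result is read. The Introduction says that HIPI was not powered for groups such as Māori, and that this trial should inform a national programme. If the trial is described as having 80% power for a 26% effect, a non-significant result could be taken as evidence against an effect that the trial may have had little chance of detecting.

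**Working it through.** **1. The stated figure.** Two proportions, two-sided α 0.05 (sidedness assumed), 80% power, p₁ = 0.74·p₀, p̄ their mean:

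n = [1.96·√(2p̄(1−p̄)) + 0.842·√(p₀(1−p₀) + p₁(1−p₁))]² / (p₀−p₁)²

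Solving for n = 125 gives p₀ = 0.669 and p₁ = 0.495. Other readings:
- A one-sided test needs p₀ of about 0.60; a continuity correction needs about 0.70.
- An absolute 26-point difference needs only 32 to 57 per arm.
- A 26% reduction in odds needs about 700 to 880 per arm.

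So, with a two-sided test, a relative reduction from about 67% is the reading that returns 125.

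**2. Fall frequency from the article.** The Introduction says "there were an average of 658,000 falls annually requiring some form of medical treatment", gives a population of 5 million, and puts more than half of the falls at home where the setting was defined. Section 3.3.2 gives 3.1 consenting participants per Māori household in HIPI. Follow-up of 2 to 3 years covers the two-year hypothesis and the calendar dates in section 3.1. Home shares of 50% and 60% are assumptions.

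658,000 / 5,000,000 = 0.1316 treated falls per person-year. Multiplying by home share, 3.1 and years gives μ, the mean per control household. The proportion with any fall is 1 − exp(−μ).

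**3. Power for the primary analysis.** SE(log RR) = √[(1 + 1/0.74)/(125μ)]; power = Φ(0.3011/SE − 1.96).

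| Home share | Years | μ | Any fall | SE | Poisson power | Power for the percentage (26% relative) |
|---|---|---|---|---|---|---|
| 50% | 2 | 0.408 | 34% | 0.215 | 29% | 33% |
| 50% | 3 | 0.612 | 46% | 0.175 | 40% | 49% |
| 60% | 2 | 0.490 | 39% | 0.196 | 34% | 39% |
| 60% | 3 | 0.734 | 52% | 0.160 | 47% | 58% |
| 100% (extreme) | 2 | 0.816 | 56% | 0.152 | 51% | 63% |
| 100% (extreme) | 3 | 1.224 | 71% | 0.124 | 68% | 85% |

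Eighty per cent power needs (1 + 1/0.74)·(2.80/0.3011)² ≈ 204 control-arm falls, or about 1.63 per household. The 50% to 60% rows imply 125 × 0.408 = 51 to 125 × 0.734 = 92. With those numbers, the rate ratio detectable at 80% power is about 0.51 to 0.62.

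**4. A check that needs no baseline rate.** HIPI's interval gives SE = (ln 0.94 − ln 0.58)/3.92 = 0.123, while 80% power at 0.74 needs 0.3011/2.80 = 0.107. The Discussion speaks "of the 436 homes modified in the HIPI study". Scaling by the square root of homes per arm, with or without a factor of 3.1/2.2 for household size:
- 436 homes as one arm: SE = 0.123·√(436/125) = 0.230, power 26%. With the household factor, SE 0.194, power 34%.
- 436 homes across both arms (218 each): SE 0.163, power 46%. With the household factor, SE 0.137, power 59%.

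**The case against.** A reader might infer that 125 per arm is an arithmetic error, or cannot be reached from the article's figures. That is too strong. The article may condense a fuller calculation, so the unstated control percentage is not itself a fault. The sizing sentence also does not say home falls. If all treated falls are counted, 56%, 64% and 71% of households are affected at 2, 2.5 and 3 years, which brackets the 67% needed. This objection stands. It does not rescue the primary analysis, because the outcome data are home injuries (section 3.2.2) and Poisson power is 51% to 68% even then.

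A reader might also infer that true power is known to lie between about 25% and 50%. The documents do not support that precision:
- The home share is known only as more than half, and only where the setting was recorded.
- The 3.1 counts consenting participants, whereas this trial captures everyone at the address.
- HIPI's arm sizes and follow-up are not given.
- Lower Māori claiming, the exclusions in section 3.2.1, unmatched addresses set to zero (up to 14%) and overdispersion would lower power. With a dispersion factor of 1.5 (assumed), the 50% share at 2 to 3 years gives 21% to 29%. Adjustment for prior falls could raise power.

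Finally, section 3.3.2 calls the analysis that adds HIPI's Māori households the main one, and it will have more power. The number of those households is not given. The means 2.2, 3.1 and 2.1 suggest a 10% share of HIPI households, but rounding allows roughly 0% to 20%. At 10%, with 436 homes as one arm, there would be about 125 + 44 = 169 per arm. Power would then be about 37% to 51% (50% to 60% share, 2 to 2.5 years). No firm pooled figure can be given, and the 80% in section 3.2 is in any case attached to 125 per arm.

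**Conclusion.** The mismatch is certain from the text: the power statement concerns a percentage of households, the primary analysis concerns a rate, and the 26% matches HIPI's reduction in rate. Eighty per cent power is not supported for the primary analysis at 125 per arm. None of the Poisson or scaling results above reaches it, including the extreme in which every treated fall counts as a home fall.

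The size of the shortfall is illustrative only: about 29% to 47% on the national home-fall figures and about 26% to 59% by scaling HIPI. These ranges assume two-sided testing, no overdispersion in the Poisson calculation, and national rates or HIPI's precision as stand-ins for a Māori household rate that the article does not give. The finding is a power claim attached to the wrong endpoint and probably too favourable for the right one. It is not a demonstrated arithmetic error.

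**What to change.** - Keep the existing calculation as the one made at design, add the control percentage it used, and say that it does not apply to the rate analysis.
- Add, for the Poisson analysis at 125 per arm, the power for a rate ratio of 0.74 and the rate ratio detectable at 80% power. The sponsor should use its own control rate, follow-up and dispersion. Do this for this trial alone and for the pooled analysis, stating how many HIPI Māori households are added. The proxy figures above should not be written in as trial assumptions.
- State that a non-significant result will be interpreted by whether the confidence interval excludes a 26% reduction.

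The change is text only, and enrolment is unaffected. The one cost is a less favourable stated power.

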#### 3.2.1. Defining Falls and Specific Injuries

In the context of self-reports of falls, Lamb et al. [6] recommended that a fall should be defined as ‘‘an unexpected event in which the participants come to rest on the ground, floor, or lower level’’ and participants in studies using self-reported falls were recommended to be asked “In the past month, have you had any fall including a slip or trip in which you lost your balance and landed on the floor or ground or lower level?’’ These guidelines were used to classify injuries from the ACC claims data.

Key information on fall injuries is provided by a free text field on the ACC claim form to describe what happened, generally a single sentence. Using these text descriptions in conjunction with other fields in the ACC claims data, coders will classify injuries as either falls or injuries specific to the package of modifications [10]. As well as referring to the text descriptions, coders consider the fields listing the activity immediately preceding the injury (e.g., running/walking), the “cause” (e.g., tripping or stumbling), any contact with objects/people/animals (e.g., ground/floor), any “external agency” (e.g., stairs/steps) and a general injury diagnosis (e.g., contusion). These fields help identify the specific injuries, which are those potentially preventable by the package of modifications applied, including virtually all injuries occurring on outside steps and most falls occurring in bathrooms.

Generally, the specific injuries are a subset of the fall injuries. Some injuries classed as specific occur from loss of balance not necessarily resulting in the subject being on the ground or floor. Such injuries occur when balance is lost and the subject collides with an object, causing injury, or some musculoskeletal injury occurs, such as muscle/tendon/ligament strain, as a consequence of loss of balance. The specific injuries generally exclude those arising from gardening, trips on furniture or children’s toys. Consistent with loss of balance, as an essential aspect of the Lamb et al. [6] falls definition, we exclude injuries occurring when the subject was jumping (such as trampoline injuries), undertaking sporting activities, or deliberate injuries (e.g., being pushed).

Falls in garages, falls from ladders and vehicle injuries (falls from bikes or cars) are excluded as these are not normally classified as injuries occurring in the home setting. We also exclude syncopal falls where the subject fainted and was consequently injured, as these do not involve loss of balance in the normal sense.

As for the HIPI study, a count will be made of the number of fall injuries and specific injuries occurring during the year prior to the intervention.

#### 3.2.2. Home Injury Claims Data for Participating Addresses

Injury counts will be obtained from ACC claims data for all home injuries, excluding deliberate injuries (assaults or self-harm), matched by the address fields of participants that we provide to ACC. Any form of matching has the potential for errors. Addresses in New Zealand are commonly specified in non-standardized forms that are difficult to match precisely. ACC have an identification number that is assigned to the claimant’s address, however it is not unusual for a given address to have more than one identification number, mainly arising from different ways that suburbs and towns are specified. This in turn is related to the number of different people in the household (each of whom may specify their address slightly differently to a given health provider). For the list of participants’ addresses we provided to ACC, they in turn furnished information on the number of ACC address IDs matched to the provided addresses, which was sometimes zero. One participating household’s address was matched to 24 ACC address IDs, which was clearly an error. This household will be excluded from any analyses (see Figure 1). There were a further eight households linked to two ACC address IDs, four linked to three IDs and one linked to five IDs. There is no feasibly mechanism by which the occurrence of multiple matches could be associated with the random assignment to intervention or control groups, which occurred after participants were recruited and visited. Multiple-matching of an intervention address could be expected to attenuate any intervention effect, as no change in injury risk can be expected for unmodified houses mistakenly classified as being in the intervention group.

Another form of matching error will arise where no match is made between a participant’s address and their ACC claims for home injury, because of errors in the specification of the addresses in either database. There were 35 participants’ addresses out of a total of 252 (14%) with no matching ACC claims, which provides an upper limit of the degree of such non-matching that occurred. Of these, 13 were in the intervention group. Some of these will not be in the ACC list of addresses because no occupant has had an injury resulting in an ACC claim while at that address. In the analyses, these households will be assumed to have zero injuries, including falls and specific injuries.

### 3.3. Analysis

#### 3.3.1. Period over Which Outcomes Are Studied

Injuries in the treatment group will be studied from the date of the intervention to the median date that modifications were carried out for the controls in the given region; injuries in the control group will be studied from the median date of interventions undertaken in the treatment group in the given region until the date modifications were carried out for that household. In situations where households did not have any modifications carried out because the household could not be contacted, median dates will be used as the specified modification date. For houses for which no modifications were necessary, the date that the house was visited and assessed will be used as the modification date. A small number of houses in the intervention group were modified, but details on the dates and the precise modifications applied have been lost. For these houses, median intervention dates will be used. All analyses will be conducted according to the intention-to-treat principle.

#### 3.3.2. Estimating Injury Rates

In the HIPI study [5], participants consented to researchers analyzing their ACC injury records as a condition of being part of the study, and these were provided by ACC for the analysis. For the MHIPI study, ACC provided anonymized injury records matched to addresses we supplied to them and all household members were potentially part of the study. The ACC injury data included the age group and sex of the claimant as well as an address identifier that was matched to information on the treatment arm and details of the modification applied once address information had been removed. Therefore, we cannot estimate fall injury rates per person-time as we have no adequate denominators. Instead, we will estimate injury rates at the household level. Although the data were anonymized for the MHIPI study, meaning that the total number of people whose injuries were potentially being assessed from the anonymized address lists was unknown, the mean number of consenting participants per household from the HIPI study was 2.2 overall, 3.1 for Māori and 2.1 for non-Māori households.

The treatment effect will be estimated by the SAS [11] procedure GENMOD by fitting a Poisson model with a log link function to injury counts at the household level with an offset that is the log of the length of the time interval over which the injury count was obtained. As with the HIPI study, where prior falls were an important predictor of falls during the trial period, a covariate in the model would be a count of fall injuries in the 365 days prior to the start of the trial for the given household. As it is possible that different tradesmen carrying out the intervention may undertake the modifications in slightly different ways, with differing degrees of effectiveness, a stratum variable will also be included as a covariate that discriminates between participants in Taranaki and those in Wellington. For the main analysis drawing on additional data for Māori households from the HIPI study, the stratum variable will take a third level. As the unit of randomization, the household, is also the unit for which rates are estimated, there is no clustering to be accounted for in this analysis.

As with the HIPI study analysis, we will also analyze rates of specific injuries (specific to the intervention) for the treatment and control groups, expecting the safety effect to be stronger for these injuries than for fall injuries, as it was for the HIPI study.

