Outcomes studied when assessing fall prevention measures are often problematic as they require self-report of incidents, a measure that is subject to various recall-related issues that potentially affect the estimate of effectiveness [6]. A relatively complete record of medically-treated injuries avoids many such limitations. New Zealand has a national no-fault personal injury insurer, the Accident Compensation Corporation (ACC). ACC covers most of the treatment costs for injuries (regardless of fault) provided by doctors, dentists, physiotherapists, specialists, counsellors and other health professionals and 80% of lost earnings apart from the first week absent from work. Where the co-payment provided by ACC is insufficient to cover costs, the patient pays an additional surcharge. Although the ACC data provide a near-complete set of records of injuries requiring some form of medical or dental treatment, lower levels of access to medical treatment can lead to lower claim rates that underrepresent the underlying injury rates, as has been noted for Māori, for example [7]. Despite these minor limitations, ACC data provide a highly suitable outcome measure (counts of injuries receiving medical attention) to test the hypothesis that occupants of homes receiving the package of modifications will have a lower rate of home fall injuries over a subsequent two-year period.

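### Prior falls enter the log-link model as an untransformed 365-day count; log(1 + count) costs one line of code and gives an equally or more precise rate ratio, and the two descriptions of the baseline window should be aligned

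*Protocol article*

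**What the plan says.** Section 3.3.2 (Estimating Injury Rates) estimates the treatment effect by "fitting a Poisson model with a log link function to injury counts at the household level with an offset" equal to log follow-up time. Besides arm it has two covariates: stratum and prior falls. The latter is described as "a covariate in the model would be a count of fall injuries in the 365 days prior to the start of the trial", and the sentence goes on to tie that start to the individual household. The reason given is the HIPI study, "where prior falls were an important predictor of falls during the trial period". No transformation, grouping or cap is mentioned.

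Section 3.2.1 (Defining Falls and Specific Injuries) describes the baseline count differently: "a count will be made of the number of fall injuries and specific injuries occurring during the year prior to the intervention".

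The sample size paragraph in section 3.2 reads "In order to detect a change of 26% in the percentage of households with medically-treated injuries arising from falls" ("α of 0.05, 80% power") and arrives at "a sample size of about 125 households in each of the two arms". It gives no control percentage, fall rate or measure of variation between households.

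**The concern.** Under a log link, a linear count x enters the rate as exp(bx). Each additional prior fall multiplies the expected rate by the same factor, so a home with four prior falls gets exp(4b). That is steeper than persistent differences between homes would produce, and the few homes with high counts then weigh heavily on b.

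Prior falls is the only household risk predictor in the model. Randomisation protects the treatment effect from bias, so the covariate is there for precision, and with about 250 homes there is little to spare. A form that tracks household risk less closely gives some of that precision away.

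The anchor is a second, smaller matter. Control homes were modified from late 2016 to early 2017 (section 3.1), and section 3.3.1 ends their follow-up on that date. Read literally, the year before the intervention is, for controls, the last year of the outcome period.

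**Working it through.** **Inputs from the protocol.** About 125 homes per arm, a 26% change, alpha 0.05, power 80% (section 3.2). Follow-up is described as two years (Introduction); the dates in section 3.1 suggest nearer 2.5. **Assumed, because not given:** 0.15 to 1.0 falls per home-year, and between-home variance of the relative rate k = 0.5 to 2.

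**1. The plan's own figure.** Without a control percentage, 125 cannot be derived; it can only be solved backwards. With p2 = 0.74 p1 and the usual two-sided formula

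n = [1.96 √(2 p̄ q̄) + 0.84 √(p1 q1 + p2 q2)]² / (p1 − p2)²,

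p1 = 0.67 gives p2 = 0.496, p̄ = 0.583 and n = (1.367 + 0.578)² / 0.174² ≈ 125. So 125 per arm implies that about 67% of control homes have a fall injury. (A one-sided test would imply 60–61%. A 26-point absolute drop would need only about 32–57 per arm for control percentages of 30–60%.)

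**2. Implied fall rate.** With gamma heterogeneity, P(at least one fall) = 1 − (1 + kλT)^(−1/k). Setting this to 0.67 with k = 1 gives λT = 1/0.33 − 1 = 2.03, so λ is about 0.8 per year over 2.5 years or 1.0 over 2 years. With k = 0.5 and T = 2.5, λ is about 0.6.

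**3. Shape of the relation.** If household rates are gamma with shape a = 1/k, the expected future rate given x prior falls is proportional to a + x. At a = 1 that is 1 + x, so log(1 + x) with slope 1 is the true form. Four prior falls then mean 5 times the rate of none. A linear term matched to the doubling from 0 to 1 would give 2⁴ = 16 times. (A fitted slope would be a compromise; this only shows the difference in shape.)

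**4. How often the forms differ.** For x = 0 or 1 the two covariates are the same up to scale. With k = 1, P(x ≥ 2) = [λ/(1 + λ)]² in one year: 2% at λ = 0.15, 5% at 0.3, 11% at 0.5 and 20% at 0.8.

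**5. Simulation.** 1,500 trials per scenario, 250–252 homes, rate ratio 0.74, 2.5 years, gamma household rates driving both baseline and follow-up counts; Poisson fit with arm, stratum and prior falls. Empirical variance of the log rate ratio relative to the raw one-year count:

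| Falls per home-year | k | log(1 + 1-year count) | log(1 + 3-year count), same occupants |
|---|---|---|---|
| 0.15 | 1 | 0.99 | 0.95 |
| 0.3 | 0.5 | 0.997 | 0.96 |
| 0.3 | 1 | 0.975 | 0.87 |
| 0.3 | 2 | 0.90 | 0.73 |
| 0.6 | 1 | 0.92 | 0.74 |
| 1.0 | 1 | 0.87 | 0.63 |

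Further runs for the one-year log form gave 0.89 to 0.94 at 0.8 per year with k = 1, 0.71 to 0.74 at 0.8 with k = 2, and 0.98 at 0.6 with k = 0.5. With lognormal heterogeneity at 0.3 per year and k = 1 the standard error did not change (0.2090 against 0.2093).

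**6. Bias.** The mean log rate ratio was about −0.30 under either form, and ln 0.74 = −0.301.

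**7. What the planned model would report.** At 0.3 per year and k = 1 the model-based Poisson standard error is 0.1604 (raw) and 0.1601 (log). At 0.8 per year and k = 1 it is 0.098 under every form, while the true standard error lies between 0.118 and 0.143 depending on form and window.

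**The case against.** The strongest reply is that this is a preference. The protocol names the covariate and does not say that it enters linearly; functional form is commonly left to an analysis plan, which is not shown. Neither form is biased. At low rates nearly all homes have 0 or 1 prior falls and the choice hardly matters. The claims had already been supplied, so a late change could weaken pre-specification. Most of this stands, and it limits the point to a small, nearly free improvement. The timing objection is met by recording the change before outcomes are compared by arm.

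Three stronger readings are tempting, and the document supports none of them.

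- **The raw count fits poorly.** The protocol reports no count distribution and no fit. The advantage is exact under gamma heterogeneity and was absent in the lognormal check at 0.3 per year.
- **The change narrows the confidence interval.** Under the Poisson model as written, with no scale or robust variance stated, the reported standard error barely moves. What falls is the true sampling variance.
- **A three-year look-back is almost free.** It carries most of the larger gains in the table, but claims are linked by address (section 3.2.2) and eligibility requires only intended future residence (section 2.1.2), so earlier years may belong to other occupants. At 0.3 per year and k = 1 the ratio rises from 0.87 to 0.94 if 30% of the earlier history is unrelated, and to 0.99 if 60% is. It would also need a new claims extract and a matching window for the pooled HIPI households.

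On the anchor, section 3.3.2 already refers to each household's own start, so a baseline year inside control follow-up is unlikely to be intended. The two sections still differ in wording.

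**Conclusion.** The point holds as an efficiency improvement to the primary model. Replacing the raw count by log(1 + count) was never materially worse and leaves the estimand unchanged, since with a log link the rate ratio does not depend on which baseline covariate is adjusted for.

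The reduction in true sampling variance is about 0–3% at 0.15–0.3 falls per home-year with moderate dispersion (k up to 1). It is about 6–13% at 0.8–1.0 per year with k = 1, the rate implied by 125 homes per arm; that is like 6–15% more homes (1/0.94 = 1.06, 1/0.87 = 1.15). If the same 67% is reached with k = 0.5 the gain is only about 2%. With k = 2 it is about 10% at 0.3 per year and 26–29% at 0.8.

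These sizes rest on assumed rates and dispersion and on household risk that persists from baseline into follow-up. The rate inferred from the sample size further assumes a two-sided test and a relative reduction. The mismatch in the baseline anchor needs no assumption; it is a matter of wording.

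**What to change.** 1. In section 3.3.2, state that prior falls enter as log(1 + number of fall injuries in the 365 days before the household's follow-up start), and use the same form for the pooled HIPI households. Cost: one line of SAS and no new data. Record it before outcomes are compared by arm; the raw count can be kept as a sensitivity analysis.
2. Align section 3.2.1 with section 3.3.2, so that the 365-day window ends at each household's follow-up start, as section 3.3.1 defines it, in both arms. Cost: one sentence.
3. Report a robust or overdispersion-scaled standard error; without it the gain will not show in the interval. Cost: one option in the same procedure.
4. Optionally, and only as a sensitivity analysis, use a longer look-back if older claims can be obtained and, preferably, residence in those years confirmed. Cost: a further claims extract and re-linkage, and a separate term for HIPI if only one year is held there.
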